### Objectives

The overall objective of this study is to determine how changes in circadian behavior and metabolic health indicators are associated with reproductive health outcomes in females with overweight or obesity who are attempting to conceive within the HELMS program. Additionally, this study seeks to identify associated risk factors and explore the biological mechanisms underlying these relationships. We hypothesize that desirable changes in circadian behavior and metabolic health indicators are associated with favorable reproductive outcomes in preconception females with overweight and obesity. These changes are expected to correlate with specific characteristics of the females and are accompanied by concurrent alterations in the expression levels of specific genes, particularly those related to circadian rhythms, metabolism, and fertility. The specific objectives are:

To examine the association between changes in circadian behavior (meal and sleep timing) and metabolic health indicators (BMI, body fat composition, and metabolic biomarkers) over a 3-month period, and subsequent reproductive outcomes (clinical pregnancy rate and fecundability) within one-year of conception attempts among preconception females with overweight or obesity.To identify baseline socio-demographic and lifestyle factors associated with changes in circadian behavior and metabolic health indicators among these females.To explore the relationship between concurrent changes in circadian behavior and metabolic health indicators, and gene expression levels.

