### Gene expression analysis

Peripheral blood samples for gene expression analysis are collected in Tempus blood ribonucleic acid (RNA) tubes, from which total RNA will be extracted. RNA sequencing will be conducted on a selected subset of samples to identify candidate genes. Subsequently, reverse transcription-quantitative real-time polymerase chain reaction will be performed on all other samples to validate these findings. To quantify changes in gene expression, the 2 − ΔΔCt method will be used, comparing gene expression levels at baseline with those at the 3-month follow-up.

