To examine the associations of circadian behavior and metabolic health indicator changes with fecundability, we will use discrete-time proportional hazards models. These models analyze time-to-pregnancy on a discrete scale (number of menstrual cycles-at-risk during active pregnancy attempts), to estimate the hazard ratio of fecundability, termed as the fecundability ratio, along with a 95% confidence interval [31]. Adjustments for potential covariates will be made, similar to those used in the above Poisson regression models [6, 12, 29, 30]. Unlike the hazard ratio for mortality or morbidity where a ratio of < 1 is desirable, a fecundability ratio of < 1 indicates an undesirable outcome which suggests delayed pregnancy. We will account for left truncation by basing our analysis on risk sets for observed cycles at risk, considering only the cycles actively attempted during the study period. For instance, if a participant has been trying to conceive for four cycles at study entry and achieves pregnancy after seven cycles, only the cycles from the fifth to the seventh will be included in the analysis. Participants will be censored in the analysis if they do not conceive after 12 months from recruitment, start fertility treatment, cease trying to conceive, or are lost to follow-up.

To analyze the associations of socio-demographic and lifestyle factors with circadian behavior and metabolic health changes, we will employ multivariable linear regression for continuous outcomes and multinomial logistic regression for categorical outcomes, adjusting for potential covariates. For the assessment of changes in circadian behavior and metabolic health indicators with gene expression levels, we will utilize independent t-tests or Mann-Whitney U test to evaluate differences in gene expression between groups categorized by high versus low health indicators, determined by median thresholds at each time point. Additionally, correlation testing (Pearson or Spearman) will identify associations between these variables and gene expression. Corrections for multiple testing, such as Bonferroni or false discovery rate, will be applied to reduce the Type I error rate.

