### Sample size

To address the primary aim based on the assumption to detect a medium effect size of 0.4 standard deviation (equivalent to approximately a one-unit change in BMI) in changes of circadian behavior or metabolic health indicators from baseline to 3-month, we calculated that a sample size of 198 females is required. This sample size is supported by findings from previous trials that employed the healthy plate concept or a digital intervention alone, both components of the HELMS intervention, which demonstrated significant reductions in BMI exceeding one unit over a 3-month period [32, 33]. The calculation was based on achieving 80% statistical power and maintaining a two-sided type I error rate of 5%, under the assumption that 50% of the cohort will become pregnant within the year. To account for a potential 30% incomplete 3-month follow-up (including an estimated 15% pregnancy rate within 3 months) and parameter uncertainty, we will enroll a total of 283 participants.

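### One of the two gene-expression analyses splits women at the median indicator level at each visit, unadjusted, so it does not test the objective on concurrent changes

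*Protocol article*

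**What the plan says.** The third aim in the Objectives section is "To explore the relationship between concurrent changes in circadian behavior and metabolic health indicators, and gene expression levels". The hypothesis stated just before it expects indicator changes to come with simultaneous alterations in gene expression.

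The Gene expression analysis section sets the assay up for change. It uses the 2^−ΔΔCt method, "comparing gene expression levels at baseline with those at the 3-month follow-up", and Table 1 schedules expression at those two visits only.

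The Statistical analysis plan section introduces the gene analysis as an assessment of changes and then names two analyses:

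- A group comparison: "we will utilize independent t-tests or Mann-Whitney U test to evaluate differences in gene expression". The women compared are described as "groups categorized by high versus low health indicators, determined by median thresholds at each time point".
- A correlation: "Additionally, correlation testing (Pearson or Spearman) will identify associations between these variables and gene expression".

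On multiplicity it says "Corrections for multiple testing, such as Bonferroni or false discovery rate, will be applied". No covariates are named for either analysis. The sentence on risk factors, immediately before, does plan adjustment: "we will employ multivariable linear regression for continuous outcomes and multinomial logistic regression for categorical outcomes, adjusting for potential covariates".

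**The concern.** A threshold set separately at each visit classifies levels. A woman who improves a great deal but remains above the median is high at both visits. Because the median belongs to the sample at that visit, a woman can also change group when her own value has not moved. The group comparison is therefore about differences between women at one visit, whereas the objective is about movement within women.

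Two errors follow if the expression compared is the level at that visit. A gene whose expression follows a woman's improvement can be missed. A gene that differs stably between women with high and low indicator values can be reported as though it accompanied change.

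Splitting at the median also discards information. In addition, two-sample tests and simple correlations take no covariates, so differences in, say, age or ethnicity may be carried into the result. The models for pregnancy rate, fecundability, risk factors and trajectories are all stated as adjusted; the gene analysis is the exception.

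**Working it through.** **1. Reference sample size.** The article gives no number for the gene analysis, so the primary-aim figure serves as an illustration. The Sample size section plans to "detect a medium effect size of 0.4 standard deviation" with 80% power, two-sided 5% and half the cohort pregnant.

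- Per group: 2(1.960 + 0.842)² / 0.4² = 2 × 7.85 / 0.16 = 98.1, rounded up to 99. Total 198, as stated.
- Enrolled: 198 / 0.70 = 282.9, rounded up to 283, as stated.

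**2. Information kept by a median split.** For a normal indicator, the correlation between the indicator and its high/low version is √(2/π) = 0.798. Relative efficiency is 0.798² = 2/π = 0.637, a loss of 36.3%. At 198 women the effective number is 198 × 0.637 = 126.

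**3. Power at n = 198, two-sided 5%, before multiplicity correction.** Simulated with bivariate normal data, 20,000 replicates:

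| True correlation | Continuous (Pearson) | Median split (t-test) |
|---|---|---|
| 0.15 | 56% | 39% |
| 0.1975 | 80% | 60% |
| 0.25 | 95% | 81% |
| 0.30 | 99% | 93% |

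Check on the second row with Fisher's z, √(198 − 3) = 13.96:

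- Continuous: atanh(0.1975) × 13.96 = 2.79, and Φ(2.79 − 1.96) = 0.80.
- Split: 0.1975 × 0.798 = 0.158; atanh(0.158) × 13.96 = 2.22, and Φ(2.22 − 1.96) = 0.60.

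**4. Level against change.** Assume that each measure is a stable part plus a visit-specific part, with total variance 1 and a stable share s of 0.5 or 0.8 (assumed; the article gives none). If the stable parts correlate at a and the visit-specific parts at c, the correlation of levels at one visit is s·a + (1 − s)·c, and the correlation of changes is c. Simulated at n = 198, 10,000 replicates, with the split made at the 3-month visit:

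| Truth | s | Level correlation | Level split significant | Change-on-change correlation significant |
|---|---|---|---|---|
| Only changes related (c = 0.3) | 0.5 | 0.15 | 38% | 99% |
| Only changes related (c = 0.3) | 0.8 | 0.06 | 10% | 99% |
| Only stable levels related (a = 0.3) | 0.5 | 0.15 | 40% | 5% |
| Only stable levels related (a = 0.3) | 0.8 | 0.24 | 78% | 5% |

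**5. If the outcome compared is instead the fold change.** The article does not say which it is. Under the same model the correlation between the indicator level at 3 months and the change in expression is c√((1 − s)/2).

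- s = 0.5: 0.3 × √0.25 = 0.15, where the split has 39% power (table in step 3).
- s = 0.8: 0.3 × √0.10 = 0.095. Then 0.095 × 0.798 = 0.076; × 13.96 = 1.06, and Φ(1.06 − 1.96) = 0.18.
- If only stable levels are related, this correlation is zero, so the false-attribution risk disappears.

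On either reading, a per-visit split of levels detects a relation between changes poorly.

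**The case against.** The strongest reply is that the group comparison does not stand alone. The next sentence plans a Pearson or Spearman correlation with no dichotomisation stated. A reader might infer that the whole gene analysis throws away a third of its information; the document does not support that, because the correlation avoids the loss. A reader might also infer that the median split is the main test of the third objective. The article does not rank the two analyses.

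Nor does it follow that neither analysis addresses change. The variables in the correlation sentence may be the changes named at the start of the paragraph, and expression may be the baseline-to-3-month change from the assay section. On that reading the correlation is change against change, which is what the objective needs. The opposite reading is equally available, since the variables described immediately before are per-visit levels.

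Pairing is not shown to be ignored either. If the outcome is the ΔΔCt fold change, pairing is already inside it, and an independent-samples test between different women is the right type of test.

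Further limits are fair. The 198 belongs to the primary aim; some samples go to RNA sequencing and only the others to qPCR, so the gene-analysis number is unknown. The correlation of 0.20 is illustrative. The 2/π figure will differ for skewed or discrete indicators such as the 0 to 5 metabolic score. Adiposity is itself among the exposure indicators, so it cannot be treated simply as a confounder throughout. The objective is exploratory, and the pregnancy and fecundability analyses are untouched.

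What this leaves standing: the per-visit median split is written into the plan and does not match the aim, the correlation is undefined on levels or changes, and both are unadjusted. Named bivariate tests are a stated method, not a detail left to a fuller plan.

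**Conclusion.** The point holds for the median-split comparison: as written, it answers a question about levels between women, while the objective and the assay are about change within women. For a roughly normal indicator linearly related to expression it keeps about 64% of the information. At an assumed 198 women and a correlation of about 0.20, power is about 60% against 80%, before multiplicity correction. The larger effect is the mismatch with the aim: with the assumed stability of 0.5 to 0.8 and a change correlation of 0.3, the level split detects it in 38% to 10% of runs, against 99% for change on change.

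For the correlation, the point is narrower. It has no dichotomisation loss and may already test change against change, but the text does not say so, and it is unadjusted. The conclusion is therefore not that the third objective goes unanswered. It is that the plan does not fix an analysis that certainly answers it, and includes one that does not. This should be corrected, in proportion to an exploratory objective.

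**What to change.** Name as the main gene-expression analysis a linear regression of within-woman change in delta-Ct from baseline to 3 months on the continuous 3-month change in each indicator. Change in delta-Ct is the log2 fold change with its sign reversed, so it uses the planned assay output directly. Adjust for covariates chosen as in the other models, for example age and ethnicity, and apply the multiplicity correction already planned. If the Pearson or Spearman correlation is kept, state that it relates change to change.

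Retain the per-visit median-split comparisons as descriptive only. Adjustment for baseline delta-Ct and the baseline indicator is debatable in observational change analyses, and can be a sensitivity analysis.

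The same women, samples and assays serve. The cost is a revised paragraph and a little extra analysis, best settled before the expression data are analysed.

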**Methods:**

This prospective observational cohort study will enroll 283 females with a BMI of 25–40 kg/m² participating in the HELMS program at KK Women’s and Children’s Hospital, Singapore. Participants will be followed for one year as they attempt to conceive. At baseline and at the 3-month mark, circadian behavior will be assessed using validated questionnaires, tracking diaries, and digital wearables. Metabolic health will be evaluated through anthropometry, body fat composition, a metabolic syndrome score, and an insulin resistance index. Blood samples will be collected to analyze metabolic biomarkers and gene expression levels. We will use modified Poisson regression models to examine associations with the clinical pregnancy rate (primary outcome) and discrete-time proportional hazards models to estimate associations with fecundability (secondary outcome) within one year of conception attempts.

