**Fig. 2 Fig2:**
[figure not shown]
Study workflow and measurements. Baseline, 3-month, and 6-month visits include the administration of questionnaires or diaries, physical measurements, and blood tests. Participants track their frequency of sexual intercourse, menstrual periods, sleep, and activity using a mobile application and digital wearable while trying to conceive. The 9-month visit consists of a phone call where research staff check participants’ pregnancy status and conception attempts if no update received. Throughout the follow-up period, participants with a positive urinary pregnancy test are invited to undergo a dating scan at 6–10 gestation weeks to confirm pregnancies, with outcomes retrieved from medical records. Participants who do not conceive by 12-month will be invited to attend a medical review and referred for fertility medical treatment before withdrawal from the study

At the same visit, each participant receives a digital wearable ‘Oura Ring’ (Oura Health Oy, Finland) for continuous monitoring of sleep and activity. The participants are guided on how to use the HELMS mobile app to track dietary intake, sleep-wake patterns, sexual activity, and menstrual cycles, with a paper diary available as an alternative. Participants are instructed to promptly report any positive pregnancy tests after the baseline visit to schedule an ultrasound confirmation. Physical follow-up visits, which include the same assessments as at baseline, are scheduled at 3-month and 6-month intervals if conception has not occurred, during which conception attempts and family planning decisions are monitored. At 9-month, research staff conduct a follow-up phone call to check on conception attempts and pregnancy status. By 12-month, non-pregnant participants undergo a final health review and are referred for fertility treatment if needed.

Partner assessments are conducted once at the baseline visit during the preconception period to collect socio-demographics, medical history, chrononutrition profile, weight, height, and body fat composition; semen analysis results are retrieved from medical records, if available. Detailed data collection is summarized in Table 1.

**Table 1 Tab1:** Data collection

	Baseline	3-month	6-month	9-month	12-month
Informed consent	√				
Eligibility criteria	√				
Background characteristics^a^					
Socio-demographics	√				
Medical history	√				
Lifestyles					
Alcohol intake and cigarette smoking	√	√ ^b^	√		

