### Statistical analysis plan

We will perform statistical analyses using the Stata Statistical Software. The primary exposure of interest in this study is the change in circadian behavior and metabolic health indicators over the first 3 months of the preconception period. Although the HELMS program continues throughout preconception, pregnancy, and the postnatal period, this initial 3-month interval is pre-specified in TEMPO as the primary exposure window. This interval was selected to allow sufficient time to capture measurable changes in circadian behaviors and metabolic indicators before pregnancy-related changes occur and before substantial loss to follow-up. Accordingly, only participants who complete the 3-month assessment have a fully characterized exposure and are included in the primary analysis, ensuring correct temporal ordering between exposure assessment and subsequent reproductive outcomes.

To investigate changes in circadian behavior and metabolic health indicators between baseline and the 3-month follow-up as exposure variables, the primary analysis will include only participants who have completed the 3-month visit. To identify any potential selection bias, we will compare baseline characteristics between participants included in and excluded from the primary analysis, as well as those recruited into the TEMPO and HELMS studies alone. We will use Pearson’s chi-squared test for categorical variables and either independent t-test or Mann-Whitney U test for continuous variables.

We will examine the associations of changes in circadian behavior and metabolic health indicators with pregnancy rates using modified Poisson regression models. These models will estimate risk ratios and 95% confidence intervals, adjusting for potential covariates identified from the literature and using a directed acyclic graph [6, 12, 29, 30]. Changes in these indicators will be standardized to z-scores to facilitate comparison of the relative impacts of each exposure indicator. These indicators will be treated either as continuous or categorical exposures (e.g. by tertiles or quantiles). Sensitivity analyses will re-evaluate models with spontaneous conception and live birth as the outcomes.

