A secondary, exploratory analysis will include only participants who have not conceived by the 6-month visit to examine long-term trajectories of circadian behavior and metabolic health indicators. We will use group-based trajectory modelling to characterize these changes at baseline, 3-month, and 6-month intervals, anticipating different patterns such as later improvement, worsening, or stability over the period. Each trajectory group will be analyzed for its association with pregnancy rates and fecundability, adjusting for potential covariates.

Missing data will be handled through multiple imputation, creation of a distinct category for the variable, or exclusion of the variable if the missingness exceeds a predefined threshold (> 15%). We will further perform sensitivity analysis by including only complete data in the analysis.

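### The missing-data rule lets a confounder be dropped for exceeding 15% missing, or given a missing category, with no exception for the DAG covariates

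*Protocol article*

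**What the plan says.** All of the following is in the protocol article.

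- **Missing-data rule** (Statistical analysis plan, last paragraph): the options are multiple imputation, "creation of a distinct category for the variable, or exclusion of the variable if the missingness exceeds a predefined threshold". Exclusion applies above 15% missing. Nothing says when imputation takes precedence over the distinct category, or that any class of variable is exempt.
- **Sensitivity analysis** (same paragraph): "We will further perform sensitivity analysis by including only complete data in the analysis".
- **Confounder control** (same section): the risk-ratio models are fitted "adjusting for potential covariates identified from the literature and using a directed acyclic graph". For fecundability, "Adjustments for potential covariates will be made, similar to those used in the above Poisson regression models".
- **Design** (Abstract, Methods): "This prospective observational cohort study will enroll 283 females". There is no randomisation, so these covariates carry the confounding control.
- **Sample size**: 198 women analysed and 283 enrolled, from a 0.4 SD difference, 80% power, two-sided 5% error, 50% pregnant and 30% incomplete 3-month follow-up.

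**The concern.** The DAG puts a variable in the model because of its causal role. The missing-data rule can take it out because of how often it was recorded. These are different criteria, and the text lets the second override the first.

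The two fallback options fail to different degrees. Excluding the variable discards the observed values as well as the missing ones. Its confounding then returns in full, apart from what other covariates in the model capture. A distinct category keeps the adjustment among women with the value recorded but leaves the others unadjusted, so part of the confounding returns even when the missingness is purely random.

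The rule speaks of the variable without limiting it to covariates. Read literally, it could also remove a pre-specified exposure indicator. Because no criterion separates imputation from the distinct category, that choice could be made after the data are seen.

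**Working it through.** **1. The plan's own sample size.** With n per group = 2(1.96 + 0.84)² / 0.4², the result is 98.1, rounded up to 99. Two equal groups (50% pregnant) give 198, and 198 / 0.70 = 282.9, so 283. Both stated figures reproduce. The point below concerns bias and changes neither.

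**2. When the exclusion clause is triggered.** 0.15 × 198 = 29.7, so 30 women with a missing value (30/198 = 15.2%) are enough. Up to 198 − 30 = 168 observed values would then be set aside. If the fraction were counted over all enrolled women, 0.15 × 283 = 42.5, so 43 women.

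**3. Yardstick: the detectable effect per SD.** A 0.4 SD difference in means between pregnant and non-pregnant women corresponds to a log odds ratio of about 0.4 per SD. At 50% pregnant, the log risk ratio is about 0.4 × (1 − 0.5) = 0.20, and exp(0.20) = 1.22. A large log-link Poisson simulation with the same inputs also gives 1.22.

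**4. Size of the bias.** The article gives no confounder strength, so these are assumed scenarios, not estimates for this study. Common assumptions are a true risk ratio (RR) of 1.00 per SD of exposure, 50% pregnant, one confounder, values missing completely at random, and log-link Poisson fits in at least 400,000 simulated records.

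| Assumed confounder | Full adjustment | Dropped | Missing category, 15% missing | Missing category, 30% missing |
|---|---|---|---|---|
| Binary, exposure shift 0.4 SD, outcome RR 0.8 | 1.000 | 0.979 | 0.997 | 0.993 |
| Binary, shift 0.4 SD, RR 0.6 | 0.999 | 0.951 | 0.991 | 0.984 |
| Binary, shift 0.8 SD, RR 0.8 | 0.998 | 0.958 | 0.991 | 0.984 |
| Binary, shift 0.8 SD, RR 0.6 | 0.998 | 0.910 | 0.982 | 0.968 |
| Tertiles, correlation 0.2, log RR −0.2 per step | 0.999 | 0.971 | 0.995 | 0.991 |
| Tertiles, correlation 0.3, log RR −0.2 per step | 1.000 | 0.957 | 0.993 | 0.986 |
| Tertiles, correlation 0.5, log RR −0.3 per step | 1.001 | 0.899 | 0.982 | 0.965 |

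Complete-case fits that kept the confounder, run for the binary scenarios, gave 0.996 to 1.001. Multiple imputation was not simulated; full adjustment is the value it aims at.

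**5. On the scale of the detectable effect.** For the strongest scenario, ln(0.90) = −0.105, and 0.105 / 0.20 is about 53% of the detectable log effect. For the weakest, ln(0.979) = −0.022, about 11%. The bias falls below 1 here only because of the signs assumed; it could go either way.

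**The case against.** The strongest reply is that multiple imputation is the first option listed, so nothing shows that a confounder will be dropped. That stands: the harm is permitted, not planned. A reader might infer that the plan reintroduces confounding as such, and the text does not support that.

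A second reply is that the missing category does little harm at 15% missing. That also stands. The shift is at most about 2% in these scenarios, while the 95% interval for a risk ratio per SD with 198 women and 50% pregnant is about ±14% (1.96 × √(1/198) = 0.139 on the log scale). The exclusion clause is the main problem.

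A third concerns which variables are at risk. A reader might infer that semen, partner or wearable data are confounders bound to pass 15%. The article does not show this:

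- The DAG set is not listed.
- Under Study procedure, "semen analysis results are retrieved from medical records, if available", but the other partner assessments are described as done once at baseline, with nothing to say they are optional.
- Under Circadian behavior assessment, wearable data cross-check the self-reported circadian measures, which places them on the exposure side.
- Socio-demographic, medical and lifestyle variables are collected at the baseline visit, and the Data management section describes alerts for missing entries.

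A reader might also infer that models for different indicators would end up with different adjustment sets. That does not follow. A covariate's missing fraction is essentially the same for every indicator model within the common set of women who complete the 3-month visit.

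The planned complete-data analysis is only a partial answer, because the text does not say that an excluded variable is put back for it. The choice of method for each variable may be left to a fuller plan, but the 15% exclusion and the distinct category are stated here as permitted.

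**Conclusion.** The point holds as a defect in a stated rule. Completeness may override the DAG in choosing the adjustment set, with no exception for confounders. Dropping a true confounder gives a risk ratio of about 0.90 to 0.98 per SD where the truth is 1.00, which is roughly a tenth to a half of the detectable effect on the log scale. A missing category at 15% missing gives about 0.98 to 0.997.

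These sizes rest on assumed confounder strengths, a single confounder with no correlated covariates to absorb its effect, and values missing completely at random. That some DAG confounder will in fact exceed 15% missing is not established. The rule should be changed before analysis, but it does not undermine the design or the sample size.

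**What to change.** Amend the missing-data paragraph as follows:

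- State that DAG confounders and pre-specified exposure indicators are not dropped solely for exceeding 15% missing.
- Make multiple imputation the primary method. Put the exposure, the pregnancy outcome, time at risk and baseline auxiliary variables in the imputation model. Leave out 6-month values: that visit takes place only if the woman has not conceived, so they are absent because of the outcome.
- Remove the distinct-category option for confounders.
- Keep the complete-case analysis as the sensitivity analysis, with the same adjustment set.
- Report the fraction missing for each variable.
- For a confounder that is mostly unrecorded, report results with and without it, since imputing such a variable in about 198 women is not clearly better than omitting it.

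The cost is about one paragraph of text, slightly more imputation work and somewhat wider intervals where a variable is poorly recorded. The planned 198 analysed and 283 enrolled do not change.
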